## Abstract

**Background:**

Repetitive peripheral nerve sensory stimulation (RPSS) is a potential add-on intervention to motor training for rehabilitation of upper limb paresis after stroke. Benefits of RPSS were reported in subjects in the chronic phase after stroke, but there is limited information about the effects of this intervention within the 1st weeks or months. The primary goal of this study is to compare, in a head-to-head proof-of-principle study, the impact of a single session of suprasensory vs. subsensory RPSS on the upper limb motor performance and learning in subjects at different phases after stroke subacute and chronic phases and mild upper limb motor impairments after stroke. In addition, we examine the effects of RPSS on brain perfusion, functional imaging activation, and γ-aminobutyric acid (GABA) levels. Subjects with mild upper limb motor impairments will be tested with MRI and clinical assessment either at an early (7 days to 3 months post-stroke) or at a chronic (>6 months) stage after stroke.

**Methods:**

In this multicenter, randomized, parallel-group, proof-of-principle clinical trial with blinded assessment of outcomes, we compare the effects of one session of suprasensory or subsensory RPSS in patients with ischemic or hemorrhagic stroke and upper limb paresis. Clinical assessment and MRI will be performed only once in each subject (either at an early or at a chronic stage). The primary outcome is the change in performance in the Jebsen–Taylor test. Secondary outcomes: hand strength, cerebral blood flow assessed with arterial spin labeling, changes in the blood oxygenation level-dependent (BOLD) effect in ipsilesional and contralesional primary motor cortex (M1) on the left and the right hemispheres assessed with functional MRI (fMRI) during a finger-tapping task performed with the paretic hand, and changes in GABA levels in ipsilesional and contralesional M1 evaluated with spectroscopy. The changes in outcomes will be compared in four groups: suprasensory, early; subsensory, early; suprasensory, chronic; and subsensory, chronic.

**Discussion:**

The results of this study are relevant to inform future clinical trials to tailor RPSS to patients more likely to benefit from this intervention.

**Trial Registration:**

NCT03956407.

## Introduction

Upper limb paresis is very common after stroke, a leading cause of disability worldwide (1, 2). Interventions based on intensive, repetitive tasks training can improve motor performance (3). Over the past two decades, neuromodulation interventions, such as repetitive transcranial magnetic stimulation (TMS) (4), transcranial direct current stimulation (5), and repetitive peripheral sensory stimulation (RPSS) (6), have been investigated as potential add-on therapies to boost the effects of training in subjects with stroke.

Repetitive peripheral sensory stimulation, in particular, is a straightforward intervention designed to enhance somatosensory input. In RPSS, trains of electric pulses are delivered to peripheral nerves by surface electrodes with parameters of stimulation aimed to predominantly activate proprioceptive and large cutaneous sensory fibers (6). The intensity of stimulation is set to elicit paresthesia but minimal or absent motor responses. RPSS targets a brain sensorimotor network known to be physiologically relevant for motor performance and learning (7). Sensory information is relayed from peripheral nerves to the spinal cord, then, *via* the dorsal medial lemniscus in the brainstem, reaches the thalamus and finally, the sensorimotor cortex. Increased excitability, activity, or use-dependent plasticity of the motor cortex have been reported in healthy subjects (8–10) or subjects with stroke (11–13) after 2 h of RPSS. The connections between neurons that represent the motor area of the stimulated body segment may be strengthened, leading to enhancement of motor performance or learning (9, 14–16). Disinhibition of silent synapses by alterations in glutamatergic receptors or reduction of GABAergic inhibition, as well-activation of silent synapses and modulation of neuronal interactions (17) may mediate these effects. The presence of functional and structural connections between areas that are responsible for motor control (16) and its relationship with somatosensory afferents underlies the rationale for the use of RPSS in individuals with motor impairment, such as stroke (18).

In subjects in the chronic phase after stroke, the effect size of RPSS to improve upper limb motor function is similar to or greater than the effect sizes of other neuromodulation interventions (6). On the other hand, information about the effects of RPSS in the subacute phase after stroke is limited. While all studies in chronic subjects with mild-to-moderate upper limb motor impairments showed benefits of this intervention, only two addressed effects in the subacute stage: one reported an increase in thumb strength after one session of RPSS compared to stimulation to the level of perception (19), whereas another described more significant improvement after *subsensory* RPSS compared to *suprasensory* RPSS (20). In patients in the chronic phase after stroke, suprasensory stimulation led to greater improvements than subsensory stimulation, and the latter was used as a control intervention in patients in the chronic phase after stroke (21, 22). Therefore, the finding of greater effects of subsensory stimulation, compared to suprasensory stimulation in patients in the subacute phase (20), was surprising and raised the hypothesis that optimal intensities/doses of stimulation may be different early, compared to at a later stage after stroke. Until now, patients in the subacute and chronic stages have not been included in a single study, in order to perform head-to-head comparisons between the effects of subsensory and suprasensory stimulation at these two phases after stroke.

Neuronal excitability, activity, or connectivity undergo changes over time after stroke. For instance, motor and sensory representations near the lesion may be remapped after cortical infarcts (23). Connectivity between primary sensorimotor and secondary motor areas changes over several weeks (24). Intracortical inhibition assessed with TMS may decrease in the contralateral motor cortex early after a cerebellar stroke and increase in the chronic phase, more than 6 months later (25).

Since excitability changes over time after lesion onset, and effects of neuromodulation interventions are known to be state-dependent (19), it is expected that results of these interventions vary at different stages after stroke. It is possible that, early after lesion onset, the variability in activity or excitability during the dynamic process of spontaneous recovery contributes to a less consistent effect of neuromodulation interventions. A systematic review and meta-analysis indicated that the potential benefits of transcranial direct current stimulation might be greater in patients in the chronic than in the subacute stage after stroke (26, 27). Furthermore, constraint-induced movement therapy (CIMT), a rehabilitation intervention that increases afferent input and provides training to decrease learned non-use of the upper limb, seems to be more beneficial in the chronic than in the subacute phase after stroke considering that the EXCITE trial (28) showed significant benefits of CIMT in patients treated between 3 and 9 months post-stroke, whereas the VECTORS (29) study showed no differences in effects of this intervention, compared to usual care, on average within the first 10 days after stroke.

Data from TMS studies suggest that RPSS enhances cortical excitability in animals (30), healthy subjects (31, 32), and patients in the chronic phase after stroke affecting the corticospinal tract (24). RPSS, compared to no stimulation (sham), leads to an increase in signal intensity and in the number of voxels activated in the primary motor cortex (M1) during thumb movements, in a paradigm of functional MRI (fMRI) based on the blood oxygen level-dependent (BOLD) effect. Perfusion in M1 assessed with arterial spin labeling at rest in healthy subjects increases after RPSS (7). This finding may be explained by increased blood flow driven by enhanced neuronal activity in M1. Whether RPSS can increase BOLD activation or global/regional cerebral blood flow (CBF) in subjects with stroke at different stages remains to be determined.

Likewise, the effects of RPSS on synaptic activity or concentration of neurotransmitters are unknown. γ-Aminobutyric acid in the sensorimotor cortex has been implicated in the processing of afferent input. For instance, in healthy subjects, GABA concentrations evaluated with magnetic resonance spectroscopy predict changes in perceptual outcome after afferent, tactile stimulation of fingertips (33). In rats, GABAergic inhibition modulates responsiveness to afferent stimulation of the forepaw (34). The GABA concentration or activity in M1 may influence responsiveness to RPSS. Furthermore, RPSS may also increase or decrease GABA levels in the cortex. Until now, these hypotheses have not yet been tested.

The primary goal of this study is to compare the effects of a single session of RPSS on motor performance and motor learning in subjects with stroke in the subacute (EARLYgroup) and chronic (CHRONICgroup) phases with mild upper limb motor impairments. We hypothesize that enhancement of motor performance and motor learning by RPSS will be significantly greater in subjects in the CHRONICgroup than in subjects in the EARLYgroup, when exposed to the same experimental paradigm. In addition, we compare the effects of a single session of RPSS on cerebral perfusion, changes in the BOLD effect, and on GABA levels changes in ipsilesional and contralesional M1. Our hypothesis is that changes in these outcomes will be significantly greater after RPSS in subjects in the chronic, than in the early stage.

## Methods and Analysis

### Study Design

This is a multicenter, randomized, parallel-group, proof-of-principle clinical trial with blinded assessment of outcomes. Figure 1 summarizes the study protocol.

**Figure 1 F1:**
[figure not shown]
Experimental paradigm. NIH, national institutes of health; PHQ-9, patient health questionnaire-9; MMSE, mini-mental state exam; MRI, magnetic resonance imaging; RPSS, repetitive peripheral nerve sensory stimulation; JTT, jebsen–taylor test.

#### Location and Setting

This ongoing study is conducted in three hospitals in Brazil: Hospital Israelita Albert Einstein (HIAE, coordinating center), Hospital das Clínicas da Faculdade de Medicina da Universidade de São Paulo (HCFMUSP) both in São Paulo, and Hospital São Rafael (HSR) in Salvador. Initially, the study would involve two centers (HIAE and HSR). HCFMUSP was included as an additional center due to difficulties in patient recruitment. The coordinating center (HIAE) was responsible for the design of the protocol, submission of the project to the HIAE Ethics Committee and to the funding agency (Fundação de Amparo à Pesquisa do Estado de São Paulo, FAPESP), creation of the research forms, and management of the project. It is also responsible for the submission of amendments, for providing and assessing the training of researchers involved in the protocol, and for communication with all centers. Weekly meetings were performed between researchers from the three centers.

The first patient was included in December 2019. The study was interrupted in March 2020 due to the COVID-19 pandemic. Recruitment was restarted in São Paulo in May 2021 and in Salvador in July 2021.

The protocol is reported according to the Standard Protocol Items: Recommendations for Intervention Trials (SPIRIT) statement (Supplementary Materials).

### Participants

The inclusion and exclusion criteria are shown in Table 1. Subjects able to perform at least four of the tasks of the Jebsen–Taylor test (JTT) are included. The JTT scores the time (in seconds) required to perform activities often used in daily living: copying a sentence; turning over cards; picking up small common objects such as coins, bottle-cap, and paper clips; simulated feeding using a spoon; stacking checkers; and moving large light and heavy objects (32, 35).

**Table 1 T1:** Inclusion and exclusion criteria.

**Inclusion criteria**	**Exclusion criteria**
• Age ≥ 18 years • Ischemic or hemorrhagic stroke confirmed by computed tomography or magnetic resonance imaging, between 7 days and 3 months before enrollment (subacute phase), and at least 6 months (chronic phase) • Ability to perform at least 4 of 7 tasks performed in daily life that is part of the Jebsen–Taylor test; • Upper limb paresis contralateral to the lesion	• Inability to provide consent • Anesthesia of the paretic hand • Severe spasticity at the paretic elbow, fist or fingers, defined with a score larger than 3 on the Modified Ashworth Scale • Shoulder pain or join deformity in the paretic limb • Lesions affecting cerebellum, or cerebellar pathways in the brainstem • Uncontrolled psychiatric disease • Neurological diseases such as Parkinson disease or chronic uncontrolled chronic disease such as cancer or cardiac insufficiency • Aphasia or severe cognitive deficit

### Recruitment

Subjects are recruited in the community through advertisements on websites or social media, and from admissions to HSR, HIAE, and HCFMUSP. In the three hospitals, preliminary eligibility is assessed according to information from medical records. Information about the protocol is also sent to physicians or therapists from these three institutions and from other hospitals or clinics, to be disseminated to patients who may be interested in participating in the study.

### Subjects' Characteristics

The following characteristics are evaluated at baseline in the first experimental session (Figure 1): age, gender, ethnicity, years of education, time from stroke, type of stroke (ischemic/hemorrhagic), medications, lesion side/location, etiology of ischemic strokes according to the Causative Classification System (36) and scores in the following scales: the Modified Rankin Scale, National Institutes of Health Stroke Scale (NIHSS) (37), Modified Ashworth Scale (MAS—elbow, wrist, and finger joints) (38), Oldfield Inventory (prior to stroke) (39), Fugl-Meyer Assessment of Sensorimotor recovery (upper limb—FMA) (40), Mini-Mental State Examination (37), Patient Health Questionnaire-9 (PHQ-9) (41), and Edinburgh Handedness Inventory (39). Assessments are performed by researchers (therapists or medical students). Prior to the onset of patient recruitment, all researchers had to be certified in performance of the NIHSS (https://www.nihstrokescale.org/). After availability of a certification of the Portuguese version of the MRS (https://docs.google.com/forms/d/e/1FAIpQLSfJIzi6G9SH8VaPxqe7txcK55ApfFRVvReWV37FRaARG6PbYQ/viewform), all researchers involved in the MRS assessment were certified. A video with demonstrations of how to administer and rate each item of the FMA was produced, watched, and discussed in meetings with all researchers, prior to realistic simulations in which the researchers played roles of assessors and “patients.” Data collection only started in each center after the local principal investigator considered that characteristics of the patients and outcomes had been consistently evaluated in the realistic simulations. After the beginning of the COVID-19 pandemic, data were not collected for several months. All researchers involved in the assessment of characteristics of patients or outcomes were trained again before data collection was restarted.

An experienced radiologist defines lesion locations by the evaluation of MRI (FLAIR, T2, and T1-weighted images—see “Imaging protocol”) as: right/left; frontal/temporal/occipital/parietal/insular; corticosubcortical, cortical, or subcortical; involving or not the precentral gyrus, postcentral gyrus, centrum semiovale, corpus callosum, posterior limb of the internal capsule, thalamus, basal ganglia, mesencephalon, pons, or medulla.

At HIAE, the presence of motor-evoked potentials (MEPs) to TMS is assessed by the principal investigator, who has been trained and performed the procedure for the past 20 years, in the absence of contraindications (42). A safety screening questionnaire is filled before the procedure (43). TMS is delivered to the affected hemisphere through a figure-of-eight-shaped coil (MC B-70, outer diameter 100 mm, max dB/dt31 kT/s near the coil surface) held by an investigator, connected to a biphasic MagPro X100 (Alpine Biomed). Electromyography (EMG) activity is recorded at rest from the surface electrodes placed over the *abductor pollicis brevis* muscle in the paretic hand. EMG responses are amplified (×1,000), filtered (2 Hz−2 kHz) and sampled at 5 kHz with a computerized data acquisition system built with the LabVIEW graphical programming language (44). The intervals between TMS pulses are randomized between 5 and 7 s. If no MEPs are registered at 100% of the stimulator's output, they are considered “absent.”

### Randomization, Allocation Concealment, and Blinding

Patients are randomized to one of four groups: suprasensory or subsensory in the EARLYgroup, suprasensory or subsensory in the CHRONICgroup. The randomization sequence was created by a statistician in an Excel spreadsheet in 12 blocks of 4 patients at HIAE or HCFMUSP and in 6 blocks of 4 patients at HSR, weighted 1:1 toward the suprasensory treatment group. Randomization was stratified by phase after stroke (subacute or chronic), gender, age (18–50, 51–79, ≥80 years), side of upper limb paresis and baseline upper limb FMA scores (≤47/66 or >47/66). Randomization tables are kept in locked cabinets accessed only by the principal investigator and the researcher responsible for RPSS in each center, and password-protected files.

Researchers responsible for the evaluation of outcomes are blinded to treatment allocation. All researchers received training before the onset of data collection. Videos with instructions for administration of the JTT were produced, and realistic simulations were performed. Patients are not informed about the type of stimulation they receive (suprasensory or subsensory) and are naive to the experimental hypothesis. They are instructed not to share their perceptions about the experimental sessions with other participants and researchers.

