##### Imaging Outcomes

Before and after RPSS, GABA+ (GABA plus coedited macromolecules) levels, CBF assessed with arterial spin labeling, and task-related BOLD fMRI activation are assessed at HIAE. MRI is performed before and after suprasensory RPSS or subsensory on a 3T Magnetom PRISMA scanner (Siemens Medical Solutions, Erlangen, Germany) using a 64-channel 1H receive-only head coil, without contraindications.

A standard questionnaire is used to assess potential exclusion criteria for MRI (Supplementary Materials). The following sequences are acquired: MEGA-PRESS (48), BOLD fMRI (TR: 2,000 ms, TE: 25 ms, matrix 84 × 84, FOV 210 mm, number of slices: 42, slice thickness: 2.5 mm, voxel: 2.5 mm) and perfusion (3D GRASE Pseudo-Continuous Arterial Spin Labeling, pCASL; TR: 4,300 ms, TE: 36.76 ms, bandwidth: 2,604 Hz/Px, label time 1,500 ms, post-labeling delay: 2,000 ms). In addition, before RPSS a high resolution T1 volumetric (voxel size: 0.5 × 0.5 × 1 mm^3^, matrix size: 256 × 256, field of view: 256 × 256 mm^2^, TR: 2,500 ms, TE: 3.47 ms, TI: 1,100 ms, flip angle: 7 degrees) and after, DWI (voxel size: 2 mm, isotropic; TR:10,200 ms; TE:103 ms) and GRE (voxel size: 0.9 mm × 0.9 mm × 5 mm, matrix size: 256 × 192, field of view: 240 mm, TR: 250 ms, TE:15 ms) are acquired.

The GABA spectroscopy data are collected with MEGA-PRESS (30 × 30 × 30 mm^3^ voxel, TR 2,000 ms, TE 68 ms; water suppression band set to 4.7 ppm, and an editing band alternated between 1.9 ppm and 7.5 ppm in even and odd acquisitions; 192 averages-−96 “edit off” and 96 “edit on”) and a water reference scan using the MEGA-PRESS sequence without MEGA water suppression. Data are collected first from the right and then from the left cerebral hemispheres. Therefore, the ipsilesional and contralesional hemispheres are assessed. In each hemisphere, the region of interest is centered on the “hand knob” in the primary motor cortex (49). Patients are instructed to keep their eyes closed during imaging acquisition.

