#### Sample Size

Considering the SD of the data from Conforto et al. (22), it was estimated that to assess the primary outcome with a power of 80%, 68 patients should be included in the protocol. Considering an expected 5% dropout rate, the sample size was increased to 72. Half of the patients will have <6 months post-stroke and half, at least 6 months. Forty-eight patients will be included at HIAE or HCFMUSP and 24 at HSR.

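### The stated sequence of 18 blocks of 4 cannot serve the 48 strata that the five stated stratification factors make, so the description of the randomisation contradicts itself

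*Protocol article*

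**What the plan says.** All of the allocation method is in the section Randomization, Allocation Concealment, and Blinding. A statistician prepared the sequence in a spreadsheet. It was laid out "in 12 blocks of 4 patients at HIAE or HCFMUSP and in 6 blocks of 4 patients at HSR", and the allocation ratio is given as "weighted 1:1 toward the suprasensory treatment group". The next sentence reads: "Randomization was stratified by phase after stroke (subacute or chronic), gender, age (18–50, 51–79, ≥80 years), side of upper limb paresis". It ends with a fifth factor, "baseline upper limb FMA scores (≤47/66 or >47/66".

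The Sample Size section matches the block counts. It states "with a power of 80%, 68 patients should be included in the protocol", then "Considering an expected 5% dropout rate, the sample size was increased to 72", with half of the patients in each phase, and "Forty-eight patients will be included at HIAE or HCFMUSP and 24 at HSR".

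The article mentions no minimisation, dynamic allocation, merging of strata or hierarchy among the factors. The Statistical Analysis section names only intervention and phase group as model factors.

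**The concern.** Stratified permuted blocks need a separate run of blocks for every stratum that receives a patient. A fixed sequence whose slots equal the target sample leaves nothing over for part-filled blocks. It can therefore serve only a few strata, each filling in multiples of four. Five crossed factors in 72 patients is the opposite situation.

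At stake is whether the trial can truthfully report stratification on five factors, and whether the arms will be reasonably alike on those factors. The main hypothesis compares the stimulation effect between phases, so it rests on four cells of 72/4 = 18 patients. If blocks were opened per stratum, there is also no stated rule for a patient whose stratum has no block left.

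**Working it through.** **Inputs.** Blocks: 12 and 6, of size 4 (randomisation section). Factor levels: phase 2, gender 2, age 3, side 2, FMA 2 (same section). Sample: 68 evaluable, 5% dropout, 72 in total, 48 + 24 by centre, half per phase (Sample Size section).

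**The plan's own figure.** 68/0.95 = 71.6, rounded up to 72; 68 × 1.05 = 71.4 also rounds up to 72. Block slots: 12 × 4 + 6 × 4 = 48 + 24 = 72. The block list matches the sample exactly. The 68 itself cannot be re-derived, because the article gives no effect size or SD, but nothing here depends on it.

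**Strata against blocks.**
- Strata: 2 × 2 × 3 × 2 × 2 = 48; over two centre lists, 96.
- Patients per stratum: 72/48 = 1.5; by list, 72/96 = 0.75. Both are well below one block of 4.
- One block per stratum would need 48 blocks (192 slots), or 96 blocks (384 slots) by list.
- At most 18 strata can own a block, so 48 − 18 = 30 have none (96 − 18 = 78 by list).

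**Could empty strata rescue it?** Some strata will receive nobody. The article gives no covariate mix, so four were assumed, from even to very skewed, with side 50/50 throughout. For each, 10,000 samples of 72 (36 per phase) were simulated with unlimited blocks opened per stratum.

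| Age 18–50 / 51–79 / ≥80; gender; FMA | Mean blocks needed (minimum), lists ignored | Patients in complete blocks | Mean blocks needed (minimum), two lists | Patients in complete blocks |
|---|---|---|---|---|
| thirds; 50/50; 50/50 | 38.4 (29) | 17% | 49.9 (40) | 5% |
| 25/65/10; 50/50; 50/50 | 34.7 (27) | 33% | 44.7 (34) | 13% |
| 15/80/5; 40/60; 30/70 | 31.4 (24) | 48% | 39.0 (30) | 27% |
| 10/88/2; 35/65; 15/85 | 28.6 (22) | 60% | 34.0 (26) | 43% |

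Eighteen blocks never sufficed. Even in the most favourable cell, complete blocks number 0.60 × 72/4 = 10.8 of 28.6, so most blocks stay incomplete.

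**Balance if blocks are opened per stratum without limit.** The SD of the overall difference in arm size is 4.4 to 6.3 with lists ignored and 5.4 to 7.3 with two lists. Simple randomisation gives √72 = 8.5.

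Per phase of 36, a further assumed mix was used: 45% women, ages 25/65/10%, side 50/50, 35% with FMA ≤47, and 24 + 12 patients per phase on the two lists. The mean absolute arm difference is about 3.8, with a chance of about 29% of a difference of 6 or more. Simple randomisation gives about 4.8 (√(2 × 36/π) = 4.8) and about 40%.

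**Cost in power.** The variance of an arm contrast is proportional to 1/n₁ + 1/n₂.
- 18:18 gives 1/18 + 1/18 = 0.1111.
- 21:15 gives 1/21 + 1/15 = 0.1143, a ratio of 1.029. A contrast with 80% power falls to about 79%.
- 22:14 gives 1/22 + 1/14 = 0.1169, a ratio of 1.052, and about 78%.

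**What 18 blocks can serve.** Centre list × phase: 48/2 = 24 patients = 6 blocks per phase, and 24/2 = 12 patients = 3 blocks per phase. So 6 + 6 + 3 + 3 = 18, provided that each list enrols half its patients in each phase. The article fixes that split overall, not by centre.

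**The case against.** The strongest reply is that a journal article condenses a fuller project document, which may describe minimisation or a partial hierarchy of factors. That is possible, so one cannot say outright that a report of stratification on five factors would be untrue. But the point is not a missing detail. The article states both the block counts and the factors, and the two do not fit. A fixed list prepared in advance and kept as tables also sits poorly with minimisation.

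One could also read the block counts as repeated within every stratum. Their exact match to 48 + 24 patients argues against that.

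The second reply is that little harm follows. This largely stands. Allocation remains random on either reading, so no bias or invalid test is shown, and the power loss is one or two percentage points.

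A reader might go further in four ways that the documents do not support:
- **That incomplete blocks remove the benefit of blocking.** They weaken it; the simulated balance is still better than simple randomisation.
- **That arm balance among imaged patients is unprotected**, because "task-related BOLD fMRI activation are assessed at HIAE" while HIAE is grouped with HCFMUSP in the block counts. The text does not say how that list is shared, nor that HCFMUSP patients go without imaging.
- **That imbalance on FMA matters most because it is the leading prognostic factor.** The article does not rank the factors.
- **That blocking by list and phase would remove imbalance altogether.** That needs an exact phase split within each list and fixed blocks of 4.

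**Conclusion.** The contradiction is established by counting alone: 18 blocks, 48 strata (96 by list), and at least 30 of 48 strata without a block. A permuted-block scheme stratified on all five factors cannot be run with this list. Either the stratification was not done as described, or blocks were opened per stratum and the list runs out.

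The size of the consequence depends on assumed covariate mixes. Under the mix used, the mean arm difference per phase is about 3.8 against 4.8 for simple randomisation, and a 21:15 split costs about 3% in variance. The practical harms are chance imbalance on the named factors and an inaccurate account of the method. It is tempting to treat this as a fault that undermines the comparison, but random allocation is intact, so it is a correction worth making rather than a condition of validity.

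**What to change.** 1. Correct the randomisation section to state which factors the 18 blocks were actually nested in, or what other method was used, including for patients already randomised.
2. For patients not yet randomised, block only within centre list × phase, or use minimisation over the same five factors. Prepare a few spare blocks: if the larger list enrolled 26 and 22 by phase, for example, it would need 7 + 6 = 13 blocks rather than 12.
3. Add gender, age, side of paresis and baseline FMA as covariates in the model in the Statistical Analysis section, and keep phase as the GROUP factor. All are already collected at baseline.

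The cost is a mid-trial amendment, with ethics approval, and possibly two allocation schemes within one small trial; the number already enrolled is not stated. If blocking by list and phase is chosen, gender, age, side and FMA are handled by adjustment rather than by design. Step 1 comes first, because what was actually done decides how much of step 2 is needed.
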